#### Participant retention

In the context of suicidal crises, spontaneous improvements or treatment discontinuations often occur, e.g. because the life conditions of the patients have spontaneously changed. Nevertheless, we make every reasonable effort to retain each randomized intent to treat participant in the study. A telephone appointment between the end of the treatment and the session that takes place 4 weeks later will serve as means to maintain contact with the patients and to optimize retention to post-discharge assessments (t_3_).

#### Subject withdrawal criteria and procedures

In the informed consent procedure, participants are informed from their therapists that they can withdraw their consent from study participation at any time without providing reasons and with no negative consequences. However, clinical staff will ask participants to share their reasons for withdrawal in order to identify any adverse impact of study procedures and to identify any difficulties experienced by subjects during the trial. Withdrawn participants will have the opportunity to continue a regular crisis therapy on the ward if this is clinically indicated.

In addition, participants can be withdrawn from the trial by the investigators, if an exclusion-criteria is found after initial inclusion either during the screening-process or by clinical assessment. For example, a patient who develops psychotic symptoms during the course of treatment may be withdrawn from the study. The participant is then excluded from the trial and continue with a regular treatment in the clinic.

## Procedures

### Recruitment and eligibility screening

The recruitment of the study patients will be carried out according to consecutive admissions to the ward. Patients are referred from the hospital, general practitioners, or from somatic wards after suicide attempts; patients can also self-refer to the clinic setting. When there are clinical indications during the admission interview for inpatient crisis treatment, and the patient fulfils the inclusion criteria, they are verbally informed about the study and are provided with written description of the study at the same or the following day.

#### Diagnostic procedures

With a summary of all available information, the current psychiatric diagnoses are made by at least one psychiatrist and one psychologist at the time of the first admission interview. These diagnoses are double-checked after a few days of care by an independent research assistant with help of a structured clinical interview. The research assistant is a Psychologist (B.Sc.) who has been trained in the diagnostic SCID-interviews. After conducting the clinical diagnostic interview, the research assistant discusses and clinically validates the diagnostic conclusion with the therapist. All diagnostic data will be recorded directly on Case Report Forms and are considered source data.

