## Method

### Aim of the trial

The primary aim of the current study is to investigate whether CAMS reduces suicidal ideation and suicidal behaviours more than Enhanced Treatment As Usual (E-TAU) within a sample of suicidal inpatients. Secondary aims are to investigate the effects of CAMS versus E-TAU on general symptom burden, depression, reasons for living, and the therapeutic relationship. Furthermore, we plan to test the influence of various moderating variables on treatment outcomes; possible moderators will include diagnostic group (borderline personality disorder in particular), number of previous suicide attempts, treatment duration, number of therapeutic sessions, and baseline levels of psychiatric distress (see [22] for more information on previous moderators of CAMS).

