### Study sample

#### Participant inclusion and exclusion criteria

Patients with acute suicidal thoughts or behaviours are included who fluently speak and read the German language and who are capable to agree to participate in the study and provide written informed consent. Most patients are expected to suffer from affective and/or anxiety disorders and/or personality disorders. This study is only treating suicidal inpatients. The consent, legal capacity, and cognitive capacities are clinically evaluated. When participation is clinically judged to be contraindicated for a particular patient, they are excluded from the study.

Patients are also excluded who are chronically suicidal and/or have been treated in an inpatient psychiatric setting for a total of more than 12 weeks within the last 12 months, or who have been admitted more than 6 times during this period, or who live in an assisted living facility. In addition, patients with a psychotic disorder during the last 12 months, an eating disorder with BMI < 16 and/or a current substance dependence are excluded. Substance abuse or previous substance dependence are not exclusion criteria. Patients who are currently suffering from psychotic symptoms as part of an underlying depressive disorder are also excluded, as are patients with developmental disabilities, dementia or an organic condition. Patients are also excluded, who, at the time of admission, have already planned further long-term inpatient or day-clinic treatment to continue after crisis intervention therapy without being discharged in the meantime, as well as those, who have to be treated on our crisis ward for longer than 40 days. However, the duration of the treatment must be at least 10 days in order to ensure that patients receive a sufficient extent of treatment (at least three sessions following the admission interview). The exclusion criteria are established at the time of admission (t_1_) and validated by using the diagnostic interview any few days later. Patients who are committed against their will as per civil legal requirements (PsychKG of the federal state of North Rhine-Westphalia or the nationwide valid law of care) do not take part in the study.

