### Diagnosis

#### Structured clinical interview for DSM-IV Axis I & Axis II

##### SCID- I & SCID-II

The SCID-I is a diagnostic instrument based on diagnostic criteria for Axis I disorders found in the *Diagnostic and Statistical Manual of Mental Disorders*, Fourth Edition (DSM-IV-TR [41–43];). The SCID has been shown to have good reliability with kappa values ranging from .04 to .84; there is an overall mean of .61 for all disorders across a large number of samples. Test-retest reliabilities for disorders in psychiatric patients range from .54 to .84 with a mean of .73. Additionally, the *Structured Clinical Interview for DSM-IV Axis II* was used to identify participants with any personality disorder, because of the higher suicide risk associated with personality disorders, which is particularly true for patients with borderline personality disorder [44]. The SCID interviews will be conducted after the baseline assessment within the first days of study treatment.

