#### Blinding

Due to the behavioral nature of the intervention, neither participants nor therapists and therapy interpreters can be blinded. However, the diagnostic examination is performed by an independent clinician who is blinded for the study group and we tried to keep the group membership confidential from the treatment team and from other patients and study participants, e.g. there was no documentation about the group membership in the patient file. Participants are instructed not to reveal any information related to the group they have been assigned to or regarding the therapeutic process.

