#### Treatment fidelity

The therapists in CAMS and TAU are a licensed psychotherapist and a psychologist (Msc.). The assignment to the therapist is consecutive, i.e. the clinician who conducted the admission interview will also be responsible for further treatment. Potential effects of the therapists will be analysed during the evaluation and using post-hoc analyses. We trained CAMS therapists with help of the E-learning training by [name], which both therapists have completed before the start of the study. Additionally, both have worked intensively with the CAMS manual written by [name]. The administration of the Suicide Status Form (SSF) was practiced by each therapist with at least 3 patients in a pilot phase prior to the start of the study. This methodology ensured that the therapists internalized both the content and process of CAMS demonstrating sufficient adherence to the CAMS framework. In the event of difficulties, [name] provides consultation.

Every fourth treatment session of the therapists is supervised. Each therapy session is audiotaped, and the therapists are rated for adherence according to the CAMS Rating Scale (CRS) by an external evaluator so optimal treatment adherence to CAMS is ensured [46]. The supervisors also monitored the E-TAU sessions using the CRS to ensure and verify that clinicians were not doing CAMS procedures in these sessions thus ensuring experimental fidelity. The CRS is an observer rating scale and consists of three parts and 14 items in total. Part I covers the treatment philosophy, part 2 the clinical/ session framework and part 3 the overall rating. The items were rated on a 6-point scale from 0 = poor to 6 = excellent. The use of the CRS therefore serves to confirm the difference in treatment groups with regard to the fact that the same therapists are treating both groups. We discussed the problem of the CAMS therapists being also the TAU therapists and the question if how the therapy is influenced by the knowledge about the other therapy arm. But in fact, despite the risk of contamination were mitigated by review of videos and use of the CRS. Any experimental between-group differences would provide clear proof of an experimental effect as the clinicians serve as their own control (removing a tremendous source of error variance seen in other RCT’s that use different clinicians in each arm of the trial).

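### The SCID conclusion is validated with the arm-aware treating therapist after randomisation, so the diagnosis used for the borderline moderator and the later exclusion check is open to arm-aware input, even if the interview stays blind

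*Protocol article*

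**What the plan says.** All references are to the protocol article.

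- **Blinding** concedes that "neither participants nor therapists and therapy interpreters can be blinded", then states that "the diagnostic examination is performed by an independent clinician who is blinded for the study group".
- **Trial design** puts randomisation and disclosure of the arm to the patient directly after the baseline questionnaires, with treatment starting the next day.
- **SCID-I & SCID-II** gives the timing of the interview: "The SCID interviews will be conducted after the baseline assessment within the first days of study treatment".
- **Diagnostic procedures** has a research assistant double-check the admission diagnoses by structured interview, after which "the research assistant discusses and clinically validates the diagnostic conclusion with the therapist". Diagnostic data go directly onto the Case Report Form (CRF) as source data.
- **Treatment fidelity** identifies the therapist: "the clinician who conducted the admission interview will also be responsible for further treatment". It adds that "the same therapists are treating both groups".

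The diagnosis has two uses. Under **Participant inclusion and exclusion criteria**, the exclusions are set at admission and then "validated by using the diagnostic interview any few days later". Under **Aim of the trial**, "possible moderators will include diagnostic group (borderline personality disorder in particular").

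**The concern.** A blinded diagnostic examiner protects the diagnosis only if the result that is used stays free of people who know the allocation. Here the conclusion goes back to the treating therapist for validation before it is final, after treatment has begun. Three things could be affected.

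1. **The moderator.** A moderator should not depend on allocation. If borderline status can be influenced by someone who knows the arm, the borderline groups in the two arms may no longer be comparable, and a treatment-by-borderline result would be hard to interpret.
2. **The later exclusion check.** Subject withdrawal criteria and procedures lets investigators withdraw a patient if an exclusion criterion is found after inclusion. A removal that rests on the validated diagnosis would rest partly on arm-aware judgement.
3. **The assessor's own blinding.** The section on components of inpatient treatment describes the research assistant who administers the questionnaires as blind to condition. If this is the same assistant, the discussion with the therapist could reveal the arm.

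**Working it through.** The article gives no figure to reproduce, so the check sets the sections in order of time.

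| Step | Event | Section | Who knows the arm |
|---|---|---|---|
| 1 | Admission diagnoses by at least one psychiatrist and one psychologist; exclusion criteria set | Diagnostic procedures; inclusion and exclusion criteria | Nobody; not yet allocated |
| 2 | Baseline questionnaires | Trial design | Nobody |
| 3 | Randomisation; patient told the arm | Trial design; Randomization | Patient |
| 4 | Treatment starts the next day, given by the admitting clinician | Trial design; Treatment fidelity | Patient and therapist |
| 5 | SCID interview in the first days of treatment | SCID-I & SCID-II | Examiner stated to be blind |
| 6 | SCID conclusion discussed and validated with the therapist | Diagnostic procedures | Therapist; assistant if it is mentioned |
| 7 | Diagnosis used for the exclusion check and the borderline moderator | Inclusion and exclusion criteria; Aim of the trial | See step 6 |

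**What stays blind.** Step 5 agrees with the Blinding section. That section speaks of the examination, and nothing in step 6 alters how the interview was conducted.

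**What does not.** The product of step 6 is a conclusion validated with an unblinded party. Nothing in the article separates it from the conclusion reached at step 5. Direct entry on the CRF shows where data are recorded. It does not show whether the entry is fixed before the discussion or which version is analysed.

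**Is there room for influence?** The SCID section quotes a mean kappa of .61 across disorders, so diagnoses leave scope for judgement. The article describes CAMS as built on patient-defined drivers and E-TAU as centred on planning treatment of the underlying disorders and life problems. A therapist could therefore think about diagnosis differently in the two arms. This is plausible, but the article does not show that it happens.

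**Link to the analysis set.** Statistical analyses promises to analyse all participants as randomised. The sample size section randomises 72 to reach 2 × 30 = 60 in the intention-to-treat sample, a gap of 72 − 60 = 12. So the plan itself foresees randomised patients outside its analysed set. It does not say that any of the 12 would leave because of the SCID check, so 12 does not measure this problem. It shows only that a route from withdrawal to the primary comparison is open.

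**The case against.** The case on the other side is substantial, and most of it limits the point.

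- **The blinding claim is narrow.** It covers the examination only. A reader might infer that the article promises a blinded moderator and a blinded eligibility check and then breaks that promise. It makes no such promise. This stands.
- **The therapist's power is not stated.** A reader might infer that the therapist settles the diagnosis or can overrule the SCID. The text says only that the conclusion is discussed and clinically validated, and it does not say that the arm is mentioned. This stands.
- **Eligibility and first diagnoses precede randomisation.** The therapist also had a view of the patient before allocation. This limits the problem but does not remove it, because the later check can still lead to withdrawal.
- **The same therapists treat both arms.** The mechanism cannot be two groups of therapists with different habits. It would have to be one therapist thinking differently by arm. This stands.
- **The discussion does not undo the trial's blinding as a whole.** The questionnaires are separately said to be administered blind. The arm is kept out of the patient file, and participants are told not to reveal it. Nor does the article say that the independent clinician of the Blinding section and the research assistants of the other two sections are one person. This stands.
- **The primary outcome is self-reported, and the last follow-up is by post.** Any effect on it is indirect. This stands.
- **Locking rules belong in a fuller document.** This holds only in part. The finding is not a missing locking rule but a stated procedure that brings an unblinded person into the conclusion.

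**Conclusion.** The point holds in a limited form and is minor. After randomisation and the start of treatment, a stated procedure opens the SCID conclusion to input from a therapist who knows the arm. This weakens the safeguard in the Blinding section for the diagnosis that is used, though not for the interview itself. The exposed uses are one exploratory moderator among several and the post-randomisation check of exclusion criteria.

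The documents give neither a borderline rate nor a rate of changed diagnoses, so no size can be computed. Any percentage would only restate an assumption.

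The conclusion rests on two readings: that the validated conclusion, not the SCID result before discussion, is what gets used; and, for the assessor's own blinding only, that the same research assistant interviews and administers the questionnaires. The text suggests both but states neither. A reader might go on to infer that the BSS comparison is biased. The documents do not support that. The only routes to it are withdrawals based on the validated diagnosis and possible unblinding of whoever administers a self-report scale.

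**What to change.** 1. Record and date the SCID-I/II conclusion on the CRF before any discussion with the therapist. Use that version, or the admission diagnosis made before randomisation, for the moderator analysis.
2. Keep the arm out of the discussion. Store the clinically validated diagnosis separately, for care.
3. Keep every randomised patient in the as-randomised analysis, whatever the later check finds. Locking the SCID result would not achieve this by itself, so it needs its own statement.
4. If the validated diagnosis is analysed after all, say in the Blinding section that the final diagnosis is not blinded.

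For patients already assessed, state which diagnosis is analysed.

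The cost is one dated CRF field and some wording, with no extra staff or interviews. The downside is that research and clinical diagnoses may sometimes differ. Clinical validation has value, since the interviewer is a psychologist at B.Sc. level. For that reason the locked SCID result is proposed for the moderator analysis and not as the sole basis for eligibility.

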### Diagnosis

#### Structured clinical interview for DSM-IV Axis I & Axis II

##### SCID- I & SCID-II

The SCID-I is a diagnostic instrument based on diagnostic criteria for Axis I disorders found in the *Diagnostic and Statistical Manual of Mental Disorders*, Fourth Edition (DSM-IV-TR [41–43];). The SCID has been shown to have good reliability with kappa values ranging from .04 to .84; there is an overall mean of .61 for all disorders across a large number of samples. Test-retest reliabilities for disorders in psychiatric patients range from .54 to .84 with a mean of .73. Additionally, the *Structured Clinical Interview for DSM-IV Axis II* was used to identify participants with any personality disorder, because of the higher suicide risk associated with personality disorders, which is particularly true for patients with borderline personality disorder [44]. The SCID interviews will be conducted after the baseline assessment within the first days of study treatment.

### Intelligence

#### Mehrfach-Wortschatz-Intelligenztest (MWT-B)

The Mehrfach-Wortschatz-Intelligenztest [45] is used to measure the general intelligence level according to a simple and reliable scheme using verbal material. Patients are asked in each of the lines to find out if any of the words presented actually exist and to cross it out. In each line, according to the multiple-choice principles, there is one word known in common or scientific language among four fictitious new constructions. The total of 37 items are arranged according to the level of difficulty. The total number of correctly marked lines is compared with the performance of a representative sample of German-speaking adults aged 20 to 64 (*n* = 1952). Then standards (IQ, standard value and percentile rank) can be determined.

See Fig. 2 with all standard protocol items (SPIRIT) for an overview of the procedures of the clinical trial including enrolment, diagnostic and interventions and Appendix 4 for the SPIRIT checklist.

**Fig. 2 Fig2:**
[figure not shown]
Standard protocol items (SPIRIT) for the clinical trial including enrolment, diagnostic assessments and interventions

### Interventions

#### Collaborative Assessment and Management of Suicidality (CAMS)

In brief terms, CAMS is a suicide-focused psychotherapeutic approach that targets suicidality as the primary focus of all clinical assessment and treatment. CAMS is organized around the assumption that suicidal thoughts and actions are less a symptom of a mental disorder than an intrapersonal, logical, and often compelling response to psychological stress and suffering. Suicidality can be a great challenge for the therapeutic relationship as it often fosters an opposing dynamic (patient versus therapist) over the struggle to determine whether suicide is an option or not. CAMS is intended to circumvent this adversarial dynamic by enabling the patient and clinician to constructively deal with the patient’s suicidal tendencies within a non-combative and collaborative therapeutic dynamic. Within CAMS, the patient and therapist work together in a focused manner on patient-defined suicidal “drivers” which are those problems that cause the patient to consider suicide. The “collaborative” in CAMS shows itself both content wise and figuratively: Immediately at the beginning of the CAMS intervention, the therapist asks the patient to be allowed to sit next to the patient to fill in the Suicide Status Form (SSF) during the survey (“I want to see it through your eyes”, [13]), so that both can work side by side and together.

CAMS treatment follows a pre-defined format, using the SSF as a multipurpose assessment and treatment planning tool. The continuous monitoring and work on reducing the impact of patient-defined suicidal drivers also creates alternative solutions and perspectives over the course of the sessions ensuring high-quality suicide-focused treatment that also creates detailed medical record documentation. A typical treatment course in our study is characterized by employing two sessions weekly of 30–60 min duration. Every session is initiated by filling out the SSF in a side-by side manner. In the first session, approximately 20 min are used to fill out the first part of the SSF as part of the SSF Core Assessment. At the start of all interim CAMS sessions, approximately 5 minutes is used to complete the SSF Core Assessment (as a repeated measure across CAMS-guided care). A problem-focused treatment plan directly addressing the patient’s suicidal drivers is jointly developed during the first session and routinely evaluated and updated in each following CAMS session. Furthermore, as part of CAMS-guided care, a stabilization plan is developed during the first CAMS session and evaluated and improved during every consecutive session in order to increase the patient’s suicide-related coping skills. Thorough the course of CAMS-guided care stabilization and treating suicidal drivers are central to effective care. Thus, ongoing CAMS care consists of developing adequate coping skills and helping the patient identify and cope with their suicidal drivers more effectively. Within the CAMS framework, suicidal drivers are further divided in two categories; direct and indirect drivers. Direct drivers are thoughts, feelings, or behaviours that increase specific suicidal risk (e.g., being sexually abused as child or break up of a marriage). Indirect drivers are factors that do not produce acute suicidal states but instead increase the vulnerability and the potential activation of direct drivers (e.g., drinking, isolation, insomnia). The CAMS approach does not require any therapeutic orientation and does not prescribe precise interventions as to how exactly suicidal drivers should be treated, which means that the therapist rely on interventions that can treat driver problems (e.g., insight-oriented work, vocational counselling, couples therapy, exposure treatment for trauma).

There are no mandatory homework assignments during a CAMS course of care. The duration of CAMS-guided care is dependent on the treatment progress and varies between patients. The treatment is concluded when the clinician and the patient agree that the acute danger of a suicidal act is eliminated, adaptive coping skills are developed while the patient scores him/herself below 3 on subjective suicidal risk rating (on a 5-point scale) and that they are managing any suicidal thoughts or feelings while remaining behaviorally stable which may trigger discharge from the inpatient setting. In the present RCT, cases who have received between 4 and 9 CAMS sessions including the initial session will be analysed. See Appendix 2 for the complete CAMS Material.

